### Study purpose

The purpose of the study is to evaluate the effectiveness of MT4C compared to an educational control group with respect to increasing hope, general self-efficacy and HRQoL and supporting participants through their experience of transitions over time. We expect to find that family carers who are allocated to MT4C intervention group will show greater improvement in hope, self-efficacy and HRQOL, at no additional cost from a societal perspective, compared to an educational control group. MT4C will be used for 3 months and we will be looking to see if the effects continue on after use for 6 months. The study will specifically address the following research questions:Does use of MT4C result in a 3 month (immediately post intervention) and 6-month (3 months after intervention) increase in HRQoL, self-efficacy, and hope, in carers of persons with ADRD and MCC compared to an educational control group?Does use of MyT4C help carers of community-dwelling older adults with ADRD and MCC deal with significant changes they experience as carers? andAre the effects/benefits of the MT4C intervention achieved at no additional cost compared to an educational control group?

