## Methods/Design

### Study design and participants

This is a multi-site, pragmatic, mixed methods, longitudinal, repeated measures, randomized controlled trial with randomized allocation to an intervention or educational control group. Recruitment and data collection began in June 2015 and is projected to be completed by June 2017. Participant data will be collected at intake (baseline) and at 1 month, 3 months, and 6 months from the beginning of the intervention. Cost data will be collected at baseline, then at 3 months and 6 months, as the cost measurement instrument asks participants to reflect upon the previous 3 months. Qualitative and quantitative data will be collected concurrently at select time points. The qualitative data will inform the quantitative data and will be integrated in the findings phase of the study. The study features two sites, one in Alberta and the other in Ontario. The CONSORT (Consolidated Standards of Reporting Trials) statement for non-pharmacological and pragmatic interventions was used to design the study and will be used to report study findings (Fig. 1). This study received ethical approval from the University of Alberta Health Research Ethics Board (# Pro00048721) and the Hamilton Integrated Research Ethics Board (#15–309).

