### Power and sample size

A convenience sample of 180 carers of older adults with Alzheimer’s disease/related dementias and MCC will be recruited to participate in this study; 90 in Ontario, and 90 in Alberta. This sample size (45 per group × 2 groups × 2 provinces) will provide 80% power (alpha = 0.05) to detect a mean difference of 2 increases in the MCS of the SF12v2 (primary outcome) with a standard deviation of 2.5.

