#### Question 1: primary outcome analysis

Intent to treat analysis using generalized estimating equations (GEE) was selected as the analytical model. Analyses will be implemented using PROC GENMOD in SAS Version 9.3 [31]. The GEE model will include the following variables: group (intervention, control), time, group x time interaction, and selected covariates (if a significant intervention effect is detected in a model without covariates). If included in the GEE, covariates will include age, gender and other variables where significant group differences are seen in a comparison at baseline. The outcome of interest is a continuous variable SF12v2 MCS. The variable of primary interest is the group and time interaction, which indicates a treatment effect if statistically significant [32]. Time will be modelled based on assessment of a plot of the mean MCS values for both groups at each time period, with time treated continuously if a linear trend is observed and categorically if a non-linear trend is observed.

GEE does not require a normal distribution and SAS offers a number of distributional choices and associated link functions. The distribution (and link) selected will be the one that best matches the distribution of MCS scores for study participants. MCS is negatively skewed in many populations, with few suitable functional distributions for this pattern. If the distribution of MCS scores is significantly negatively skewed, a reflected transformation will be applied to the MCS scores in an effort to normalize them [33] and then the normal distribution and identity link will be applied to the transformed data in the GEE.

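### With categorical time, the primary rule rests on a group-by-time interaction that includes month 1, although Question 1 asks only about 3 and 6 months

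*Protocol article*

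**What the plan says.** Under Question 1: primary outcome analysis, the protocol article fits a GEE with group, time and their interaction to the SF-12v2 MCS and gives this criterion: "The variable of primary interest is the group and time interaction, which indicates a treatment effect if statistically significant". The coding of time is decided from a plot of the group means, "with time treated continuously if a linear trend is observed and categorically if a non-linear trend is observed". The schedule under Study design and participants is: "Participant data will be collected at intake (baseline) and at 1 month, 3 months, and 6 months from the beginning of the intervention". Categorical time therefore has four levels.

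The question to be answered is under Study purpose: "Does use of MT4C result in a 3 month (immediately post intervention) and 6-month (3 months after intervention) increase in HRQoL". The same section expects that MT4C users "will show greater improvement in hope, self-efficacy and HRQOL" compared with the educational control. Month 1 appears in no research question.

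Two further statements depend on the rule. Covariates enter the model only on a condition: "selected covariates (if a significant intervention effect is detected in a model without covariates". The Secondary analysis section applies the same analysis to PCS, HHI and GSES.

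**The concern.** A primary test should be significant when the answer to the primary question is yes, and rarely otherwise. Here the printed criterion covers every departure from parallel group profiles over four visits, while the question covers two visits. A difference present at month 1 and gone by month 3 would meet the criterion without any effect at the times asked about. It could also trigger the covariate-adjusted model. Conversely, a gain centred on month 3 is tested together with two other components and may be missed when a direct contrast would find it. If the interaction is read as three separate coefficients, any of which may be significant, the 5% error rate is not held. The same applies to the three secondary outcomes.

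**Working it through.** **Inputs from the protocol article.** 90 carers per arm (180 randomised 1:1), MCS difference 2, SD 2.5, alpha 0.05, visits at 0, 1, 3 and 6 months.

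**Assumptions, not in the article.** Two-sided testing; complete data; the same SD σ at each visit; the same correlation ρ between any two visits (0.3, 0.5, 0.7 tried); the effect patterns below.

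**The plan's own figure.** Under Power and sample size, the target is "to detect a mean difference of 2 increases in the MCS of the SF12v2 (primary outcome) with a standard deviation of 2.5", for which the article claims 80% power. A two-sample comparison gives SE = 2.5 × √(2/90) = 0.373, 2/0.373 = 5.37, and power Φ(5.37 − 1.96) = 99.97%, not 80%. With 90 per arm and a difference of 2, 80% needs an SD of 2 / [(1.960 + 0.842) × √(2/90)] = 4.79. That mismatch is a separate matter. It is used here only to show how the results change with the SD.

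**Formula.** Let d = (d1, d3, d6) be the between-group differences in change from baseline. Their covariance is [2σ²(1 − ρ)/n](I + J), where J is the 3 × 3 matrix of ones. The inverse of I + J is I − J/4, so the joint test has non-centrality

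λ = n / [2σ²(1 − ρ)] × [Σd² − (Σd)²/4],

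with 3 df and critical value 7.815. The month-3 contrast alone has z² = n·d3² / [4σ²(1 − ρ)].

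**Common scale.** Choose the unit difference so that the month-3 contrast has 80% power: z² = (1.960 + 0.842)² = 7.849. Then n / [2σ²(1 − ρ)] × (unit)² = 15.70, and λ = 15.70 × bracket, whatever σ and ρ are.

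| Pattern (months 1, 3, 6) | Bracket | λ | Joint-test power |
|---|---|---|---|
| (1, 0, 0) month 1 only | 1 − 1/4 = 0.75 | 11.77 | 83% |
| (1, 1, 1) sustained | 3 − 9/4 = 0.75 | 11.77 | 83% |
| (0.5, 1, 0.5) peak at 3 | 1.5 − 4/4 = 0.50 | 7.85 | 64% |
| (1/3, 1, 2/3) | 1.556 − 4/4 = 0.556 | 8.72 | 70% |
| (0.5, 1, 1) | 2.25 − 6.25/4 = 0.6875 | 10.79 | 80% |

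The first two rows have the same λ, so the rule is equally likely to be met by either. In 4,000 simulated trials (SD 4.79, ρ = 0.5, difference 2), a month-3 contrast required to favour MT4C was positive in 2.8% of month-1-only trials and 78% of sustained-benefit trials. The joint test was significant in 83% and 82%.

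**How this depends on the SD.** For a 1-point difference at month 1 only, 90 per arm and ρ = 0.5:
- SD 2.5: λ = 90/(2 × 6.25 × 0.5) × 0.75 = 10.8, power 80% (64% at ρ = 0.3, 96% at ρ = 0.7).
- SD 4.79: λ = 2.94, power 27%.
- SD 10 (illustrative): λ = 0.675, power 9%.

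**Power loss at the plan's own inputs.** For an effect of 2 at month 3 and 1 at months 1 and 6, with SD 2.5, the joint test has 99.8% power and the contrast 99.97% at ρ = 0.5. At ρ = 0.3 the figures are 97.8% and 99.5%.

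**Separate coefficients.** The three changes from baseline share the baseline value, so under equal correlation their estimates correlate at 0.5. With each tested two-sided at 5%, the chance of at least one false positive is about 12.5% (2 million simulated draws). With independent tests it would be 1 − 0.95³ = 14.3%.

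**The case against.** The article never says that the interaction test is joint. A GEE with baseline as reference gives separate group-by-month-3 and group-by-month-6 coefficients, which are the quantities in Question 1, and a fuller analysis plan may name them. It is true that the 3-df reading and the three-coefficient reading are alternatives, and their defects cannot both apply. But neither reading matches the question, and the point does not rest on an omission: the printed sentence says what counts as evidence, and a plan that later named a month-3 contrast would have to override it.

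MT4C access lasts 3 months, so a real month-1 difference arises during the intervention and is a genuine effect of allocation. That stands: rejecting the null there is not a false positive. It is an answer to a question that was not asked. A full effect at month 1 with none later is also an extreme pattern, used here to show what the rule admits, not what is expected.

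The power argument is limited. It depends on the rescaling and on an effect that peaks at month 3, and it is negligible at the plan's own inputs.

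A reader might also infer that a worsening on MT4C would count as a positive primary result, because the test has no direction. The article does not support that. It speaks of a treatment effect, not a benefit, and Study purpose asks for an increase, so a significant decline would answer Question 1 in the negative. Every two-sided test rejects in both directions, and a slope difference under continuous time behaves in the same way.

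**Conclusion.** The point holds as a mismatch between the printed decision rule and the research question, and only when time is categorical. Under the joint reading, a month-1-only difference meets the rule as readily as an equal sustained one (83% each on the common scale). That equality holds at any SD and any common correlation; how often either occurs depends strongly on the SD. Under the separate-coefficient reading, the error rate is about 12.5%. Loss of power is secondary: 64% or 70% against 80% for the two peaked patterns, none of substance for the sustained patterns, and very little with a difference of 2 and SD 2.5. This should be corrected before analysis, but it does not undermine the design. The results assume two-sided testing, complete data and equal correlation between visits.

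**What to change.** Under Question 1: primary outcome analysis, replace the sentence on the interaction with wording such as:

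*The treatment effect is the MT4C minus control difference in MCS change from baseline to 3 months, estimated as a pre-specified contrast from the GEE and reported with its 95% CI; a positive difference on the MCS scale favours MT4C. The corresponding 6-month contrast is also pre-specified, with the error rate across the two controlled by [stated method]. The month-1 contrast and the joint interaction test are supportive.*

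The stated method could be testing month 6 only after a significant month-3 result, or splitting alpha. The article does not rank the two times, so the choice is the trial team's. The direction should be written out because the reflected transformation allowed for skewed MCS reverses the sign of the coefficients. Apply the same contrasts to PCS, HHI and GSES.

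The cost is a short text change and two ESTIMATE statements in PROC GENMOD, with no new data. The downside is that a benefit seen only at month 1 could not be claimed as the primary result. Under a fixed order, neither could one that emerges only at 6 months.

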### Primary analysis and handling of missing data

GEE assumes that data are missing completely at random [32] an assumption that is difficult to verify [34]. In fact, all missing mechanisms are best thought of as a continuum between missing at random and missing not at random [35], with the current recommendation from experts in the field of missing data being to base the primary analysis on the missing at random assumption [36]. Thus, after the missing data have been multiply imputed, each data set will be analyzed using GEE, and the results from these multiple analyses will be pooled to obtain an overall inference.

### Secondary analysis

Secondary (health-related) outcomes to be explored include: physical functioning as measured by the SF12v2 Physical Component Summary (PCS), HHI and GSES. The analyses relating to all secondary outcomes will be the same as described above for the primary analysis. The distribution and missing patterns for each secondary health-related outcome will be examined to select the appropriate methods for the analytical model (GEE) and for handling missing data.

#### Question 2: qualitative analysis

Content analysis will be used, consistent with a qualitative descriptive approach [37]. Initially, 3–4 research team members will independently read a sample of the transcripts, label them with codes and look for similarities, differences and patterns in the data. Team members will then meet to discuss codes and develop a coding list that can be used for analysis of the remaining transcripts. The team will meet regularly to discuss, compare, corroborate, and revise codes and group them into categories describing the participants’ experience. NVivo 11 software will be used to manage and support analysis of the study data. Several strategies will be used to enhance the rigor of the qualitative analysis. Repeated, semi-structured, individual telephone interviews with carers over a 3 to 6 month period will help to ensure credibility of the data. Investigator triangulation will involve frequent team meetings to review data coding and analysis. Transferability will be supported through the use of field notes and detailed accounts of the research process. Confirmability will be supported through the use of an audit trail of study decisions.

#### Question 3: cost analysis

The cost of services will be determined by calculating the product of the units of service over the 3-month period (i.e., the quantity) by the unit cost (i.e., the price). The costs used will be based on the values indicated in the costing manuals developed for Ontario and Alberta by the Aging, Community and Health Research Unit. The total cost (with and without hospital stay) and for each of the HSSUI categories will be determined. The data will be summarized using frequencies, means, medians, and standard deviations. GEE will also be used to compare the cost data from baseline to 3 months and then 6 months for both the intervention and control groups.

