#### Cost of use of health services

The costs of use of all types of health services for all carers will be determined using a version of the Health and Social Services Utilization Inventory (HSSUI) that has been modified for this study. The HSSUI assesses costs from a societal perspective [27] which implies collecting all costs, regardless of who bears them. The broader the perspective taken, the more applicable the study is to social policy decisions.

The initial version of the HSSUI, developed by Browne and colleagues [28], has been tested for reliability and validity [29] as well as tailored to other study populations and used to gather information on service utilization [30]. The HSSUI consists of questions about the respondents’ use of services in eight areas: primary care; emergency department and specialists; hospital days; other health and social professionals; medications; laboratory services; community support services; and other services. It directs participants to reflect back over a specific time period (i.e. 3 months). The HSSUI was also designed to assess direct out-of-pocket expenditures and indirect costs. The cost data will be derived from “quantity” data reported on the HSSUI and “price” data obtained by our team from the Ontario Ministry of Health, Alberta Ministry of Health and Long-Term Care Health Data Branch Web Portal (https://hsim.health.gov.on.ca/HDBPortal). The product of the number of units of service (quantity) and unit cost (price) is total cost.

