## Discussion

This study will assess the effectiveness of My Tools 4 Care in supporting family carers as well as the cost of this intervention from a societal perspective. Although multiple internet interventions are available for family carers, this is the first to be based on transition theory. Most interventions for family carers of persons with ADRD have been developed based on stress theories and typically focus on providing information and skills with respect to become a better caregiver. MT4C was developed to focus on supporting family carers as they experience multiple transitions. Family carers have been involved at every stage of the development of MT4C and with their assistance it has been continuously evaluated for feasibility and acceptability and to determine if it meets their needs. It is a flexible multicomponent intervention that can be used throughout the caregiver journey and now the online format gives the intervention additional flexibility and portability. It is self-administered and when the study is completed it will be made available to the public for use.

Very few interventions have examined costs from a societal perspective. It was difficult to find a measure of service use so the HSSUI was adapted to carers and their caregiving experience. For example the adaptation of the HSSUI includes costs such as financial services, or lawyers’ fees. The data from the HSSUI over time, will provided important information about caregiving and the use of health and social services.

Using a mixed method design, the qualitative evaluation will provide insight into what is important and what needs to be changed in MT4C before release into the public domain. As well the qualitative data will increase our understanding of the psychosocial processes that occur during the intervention and identify potential mechanisms of the intervention as well as additional outcomes.

There is a great need for effective interventions to support family carers of older persons with ADRD and MCC living in the community. MCC adds complexity to the care provided by family carers and increases the number of transitions they experience. Transitions can significantly impact the HRQOL of family carers [4], so MT4C has the potential to improve the hope, self-efficacy and HRQoL of family carers.

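### Total cost as defined has no item for delivering MT4C, despite the societal perspective, and a claim of no additional cost needs an upper limit on the cost difference

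*Protocol article*

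**What the plan says.** All references are to the protocol article.

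- **Question.** Under Study purpose, the third research question concerns "effects/benefits of the MT4C intervention achieved at no additional cost compared to an educational control group". The expected result is greater improvement "at no additional cost from a societal perspective, compared to an educational control group".
- **Perspective.** Cost of use of health services adopts a societal perspective, "which implies collecting all costs, regardless of who bears them". The Discussion says: "This study will assess the effectiveness of My Tools 4 Care in supporting family carers as well as the cost of this intervention", again from that perspective.
- **What is counted.** Cost of use of health services defines total cost as units of service multiplied by unit cost. The units come from the HSSUI, which asks carers about their own use of services in eight areas and is also designed to pick up out-of-pocket spending and indirect costs. Question 3: cost analysis repeats the definition: "The total cost (with and without hospital stay) and for each of the HSSUI categories will be determined".
- **Inference.** The same section plans descriptive summaries, and then "GEE will also be used to compare the cost data from baseline to 3 months and then 6 months", in each arm. It gives no margin and no rule for deciding that cost is not increased.

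**The concern.** Both arms receive the same Alzheimer Society booklet (Control group; Intervention: my tools 4 care). What the intervention arm gets in addition is the MT4C website and the checklist for recording its use. Running the website takes resources, and Table 1 itself foresees technical assistance from a study administrator. Carers do not bear these costs, so a questionnaire about carers' service use will not capture them. A perspective that counts costs whoever bears them should include them.

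The cost result is meant to inform policy. If the only resource that differs by design is left out, the comparison shows whether carers' other service use changed, which is narrower than whether the benefits came at no additional cost.

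The form of inference matters too. A statement that cost is not increased needs an upper bound on the difference. The article describes a comparison and does not say what result would support the statement.

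**Working it through.** **Step 1: the passages side by side.**

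| Element | Where | Covers MT4C delivery? |
|---|---|---|
| All costs, whoever bears them | Cost of use of health services | Yes, by its terms |
| Cost of the intervention to be assessed | Discussion | Yes, by its terms |
| Eight areas of the carer's service use | Cost of use of health services | None named for it |
| Out-of-pocket and indirect costs | Cost of use of health services | No: hosting and support are not borne by the carer |
| Adaptations of the HSSUI (examples: financial services, lawyers' fees) | Discussion | No |
| Unit costs from the costing manuals | Question 3: cost analysis | No: a price cannot supply a quantity that was never recorded |

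The first two rows require an item that the remaining rows, as described, do not contain.

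**Step 2: direction and size of the effect.** Let D be the between-arm difference in mean HSSUI cost (MT4C minus control) and c the cost of delivering MT4C per participant. The societal difference is D + c, and the plan estimates D. The understatement is therefore exactly c. If c is assigned as a constant per participant, the point estimate and both confidence limits move up by c and the standard error does not change. The documents give no value for c, so none is used here.

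**Step 3: precision of the cost comparison.** The article states no cost SD, margin or power for cost, so there is no figure of the plan's to reproduce; its sample-size statement concerns the MCS only. Inputs:

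- 90 per arm (Power and sample size: 45 × 2 provinces)
- coefficient of variation (CV = SD/mean) of cost: **assumed**, 1 to 2
- one unadjusted follow-up comparison without dropout: **assumed**

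Standard error = SD × √(2/90) = 0.149 SD. 
95% CI half-width = 1.96 × 0.149 SD = 0.292 SD.

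| Assumed CV | Half-width as % of mean cost | Chance that a two-sided 5% test is non-significant if cost is truly 20% higher |
|---|---|---|
| 1 | 0.292 × 1 = 29% | 73% |
| 1.5 | 0.292 × 1.5 = 44% | 85% |
| 2 | 0.292 × 2 = 58% | 90% |

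The last column is 1 − [Φ(0.20/(CV × 0.149) − 1.96) + Φ(−0.20/(CV × 0.149) − 1.96)]. The 20% is an illustration, not a figure from the article. At a CV of 2, an observed difference of zero would still be compatible with mean cost up to 58% higher in the MT4C arm, before c is added.

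**The case against.** The strongest reply has four parts.

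1. **No passage says that a non-significant test will be read as equal cost.** This stands. The article's one significance rule, that the group-by-time interaction is the term "which indicates a treatment effect if statistically significant", is written for the MCS. Secondary analysis carries that approach to the PCS, HHI and GSES, not to cost. A reader might infer that the plan is set up to conclude no additional cost from a failed test. The text does not support that, and a decision rule may sit in a document not shown.
2. **Question 3 can still be answered.** This also stands. A GEE with group and time gives a between-arm cost contrast with a confidence interval, which can be set against a margin. A reader might infer that the question cannot be answered as planned or that the design is tilted; neither follows. The contrast does, however, need the missing cost item.
3. **The instrument is not fully visible.** The HSSUI was modified for this study, one of its areas is an unspecified category of other services, and the costing manuals are not shown. This limits what can be said about carer time, which may already fall under indirect costs, so the documents do not show that it is left out. It does not rescue delivery cost, because an inventory of respondents' service use does not record what the provider spends.
4. **The delivery cost may be small.** MT4C is already built, online and self-administered, so the cost per participant could be minor. That is possible, but the article gives no figure, and a small cost should be shown to be small.

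**Conclusion.** The omission of delivery cost is an inconsistency within the article. Its perspective and its stated aim call for the cost of providing MT4C, and its definition of total cost has no item for it. Followed as written, the plan understates the between-arm cost difference by the delivery cost per participant. The size of that cost is unknown from the documents. The finding applies to the cost items as described and assumes that the modified HSSUI does not contain a provider-side item that the article fails to mention.

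On inference the finding is more modest. The article states a one-sided question and does not tie it to a criterion. With 90 per arm, an unadjusted half-width of about 0.29 SD (29–58% of mean cost at an assumed CV of 1 to 2) means that a non-significant difference would not by itself support a claim of no additional cost. Adjustment for baseline cost or use of both follow-up times could narrow the interval, and dropout would widen it. The percentages are illustrations, not estimates.

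**What to change.** - Add a per-participant cost of delivering MT4C (hosting, maintenance, technical assistance), taken from project accounts, to total cost in the intervention arm, and show it as a separate line. Access lasts 3 months from baseline, so it belongs in the 3-month cost window.
- Report the GEE between-arm difference in total cost, in currency units, with its 95% CI.
- Set a margin in advance and claim no additional cost only if the upper limit lies below it, never from a non-significant difference. Otherwise report the interval without the claim.
- Bring in carer time on MT4C only as a sensitivity analysis, and only where HSSUI indirect costs do not already count it. Table 2 shows that the Toolkit Checklist is completed by the intervention arm alone, so valuing those minutes in the main analysis would load one arm by construction and could count the same time twice.

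The cost is one costing exercise from project accounts and a little more analysis, with no new data from participants. The price is that a conclusion of no additional cost becomes harder to reach.
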